Safety and immunogenicity data continue to be analyzed, but are in general consistent with prior experience. Approximately 70% of both one- and two-dose vaccinees had signficant aserum HAI responses. A per-protocol analysis of the challenge study data revealed influenza-like illness in 66.7% of challenged placebo recipients, 62.5% of challenged one-dose recipients (6.3% efficacy), and 31.8% of challenged two-dose recipients (52.3% efficacy); yielding a chi2 p value of 0.041 for the 3 x 2 table and a p value of 0.021 for trend with number of vaccine doses. However, examination of the data has revealed that physician exam findings were non-contributory with one exception: pharyngitis; and that the definition of pharyngitis as applied by the study physicians led to fulfillment of the criteria for “illness” in a number of essentially asymptomatic subjects. In addition, the calibration of the disposable digital thermometers used to monitor temperature was questioned, as these yielded mean baseline temperatures just over 36ºC. Setting aside physician-observed pharyngitis and using a definition of fever based on the baseline mean + three standard deviations revealed a similar, but much stronger, efficacy trend in the data: 57.1% illness in placebo recipients; 45.8% illness in one-dose recipients (19.8% efficacy); and 4.5% illness (92.1% efficacy) in two-dose recipients (chi2 p value of 0.0007 for the 3 x 2 table and a p value of 0.0003 for trend with number of vaccine doses). An analysis based on laboratory-confirmed influenza illness (which requires illness and either isolation of influenza virus or a four-fold rise in reciprocal HAI titer across the challenge interval) demonstrates 65% efficacy in the one-dose group and 100% in the two-dose group. Because the sensitivity of influenza culture has proved poor for this strain however, this analysis remains preliminary pending data from molecular detection methods and immunoflouresence studies.

The current study is being undertaken to: a) confirm the efficacy of the two-dose regimen at a 30 μg dose level, b) re-examine the efficacy of the one-dose regimen at the 30 μg dose level with refined illness criteria, and c) examine the possible efficacy of a two-dose regimen at a 15 μg dose level, which is also highly immunogenic.

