# 9.0 Analysis Plan:

This is a phase II, four-group, placebo-controlled, randomized clinical trial. Approximately 28 subjects will be treated in each group. Volunteers will either receive two 15 µg treatments separated by two weeks, one 30 µg and one placebo treatment separated by two weeks, two 30 µg treatments separated by two weeks, or two placebo treatments separated by two weeks. In the immediate post-treatment period, outcomes are pre-specified local and systemic reactions, general adverse event rates, and immune responses assessed by antibody measurements.

Forty-one (± 3) days after the first treatment, subjects who remain eligible are challenged and then followed for an additional week regarding evidence of illness (by several alternative definitions), and also concerning virologic outcomes.

All analyses will be done with SAS, version 8.2 or later, primarily PROC UNIVARIATE, FREQ, LOGISTIC (for logistic regression with challenge data), and GENMOD (SAS PROC GENMOD implements the repeated measures regression model of Zeger and Liang [48].) Chi-square tests in PROC FREQ are exact. In this phase II trial which will not be used to provide definitive evidence of efficacy or safety, p-values of 0.05 or less for two-sided statistical tests will be considered significant and multiple comparison corrections will not be used (although the rather large number of significance tests – at least as regards safety -makes it likely that the type I error rate will be somewhat elevated.

Simple methods will be used to impute missing data. For binary outcomes, such as the presence/absence of an adverse event, alternative imputations will assume the event did, and did not, occur and the results of these contrary assumptions will be compared. For continuous outcomes, such as antibody titers, last-value-carried-forward will be used except that two consecutive missing values will not be imputed.

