- A  4-fold increase in serum A/Panama/2007/99 HAI antibody titer between day 39 ( 3) and the final follow-up visit, and absent clinical disease suggesting influenza between discharge from the isolation unit and the final follow-up visit.

9.3.7 Laboratory-confirmed Influenza Illness:

A subject will be deemed to have laboratory-confirmed influenza illness if he/she meets the definitions for BOTH of:

- Influenza infection, and
- Illness (Any).

9.3.8 Analysis:

9.3.8.1 Power Considerations:

The analysis will consider both binary outcomes (e.g., illness vs. no illness; virus shedding vs. no virus shedding, etc.) and continuous outcomes (e.g., treatment group mean temperatures, tissue counts, peak viral shedding and shedding AUC, etc.). The variability, and potential magnitudes of the differences in the latter are *a priori* unknown. However, the virus challenge inoculum will be selected to yield *approximately* 50 - 60%, based on past experience, of the binary outcome “any illness.” (Closer control of this rate is difficult to ensure.) Assuming that a minimal efficacy level of 70% (where efficacy = [rate controls -ratetreated ] x 100 / rate controls) is of interest to justify further development of a given dose or formulation, it is possible to calculate that a group size of 28 will yield ≥ 0.80 power to detect a ≥ 70% reduction in the rate of the binary outcome “any illness.”

9.3.8.2 Analyses:

The analysis concerns between-group comparisons of the four cross-over groups regarding clinical and immunologic binary outcomes. Alternative definitions provide six binary clinical outcomes (fever, upper respiratory illness, lower respiratory illness, systemic illness, illness [any], and illness + infection) that can be compared between groups by chi-square tests. More flexible analyses use logistic regression (SAS PROC LOGISTIC) with the presence or absence of influenza, separately for each definition, as the outcome. Covariates are cross-over study group, age, gender, race, and, for some models, titers after vaccinations 1 and 2.

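### The adjusted illness models have no provision for an arm with no events, which is foreseeable for laboratory-confirmed illness in the two-dose 30 µg group

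*Protocol*

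**What the plan says.** Protocol section 9.3.8.2 lists six binary clinical outcomes: fever, upper respiratory, lower respiratory and systemic illness, any illness, and illness plus infection. It compares groups by chi-square tests and then adds a model: "More flexible analyses use logistic regression (SAS PROC LOGISTIC) with the presence or absence of influenza, separately for each definition, as the outcome". The terms are given next: "Covariates are cross-over study group, age, gender, race, and, for some models, titers after vaccinations 1 and 2".

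Section 9.0 names the same procedure, "LOGISTIC (for logistic regression with challenge data". Its small-sample provision covers only the unadjusted tests: "Chi-square tests in PROC FREQ are exact". The decision rule is that "p-values of 0.05 or less for two-sided statistical tests will be considered significant". No test statistic, interval method or sparse-data option is stated for the logistic model.

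Section 1.0 describes the previous challenge trial. On any illness under refined criteria it reports "57.1% illness in placebo recipients; 45.8% illness in one-dose recipients (19.8% efficacy); and 4.5% illness (92.1% efficacy) in two-dose recipients". On laboratory-confirmed illness the analysis "demonstrates 65% efficacy in the one-dose group and 100% in the two-dose group", with the caution that "this analysis remains preliminary pending data from molecular detection methods and immunoflouresence studies". The first stated reason for the present trial is to confirm the efficacy of the two-dose 30 µg regimen. Section 4.1 expects about 25 challenged subjects per group.

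**The concern.** Maximum-likelihood logistic regression has no finite coefficient for a group in which nobody has the event. The fitting algorithm moves towards minus infinity and stops where its convergence rule stops it. The printed odds ratio, interval and Wald p-value then reflect the stopping rule and not the data. The effect is perverse: the stronger the protection, the less the adjusted estimate says about it.

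The protocol's authors thought about small samples, because they made the chi-square tests exact, but they did not carry that through to the model. If the problem first appears after unblinding, a replacement method has to be chosen with the results in view.

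**Working it through.** **Inputs.** About 25 challenged per arm (section 4.1). Two-sided 0.05 (section 9.0). Previous any-illness rates of 57.1%, 45.8% and 4.5%, and 100% two-dose efficacy on laboratory-confirmed illness (section 1.0). The placebo rate of laboratory-confirmed illness is not given, so 20% to 60% is assumed.

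**The protocol's own figures.** Efficacy on any illness: 1 − 4.5/57.1 = 92.1% and 1 − 45.8/57.1 = 19.8%, as stated. The percentages fit counts of 12/21, 11/24 and 1/22, which are inferred and not printed. These give a 3 × 2 chi-square of 14.56, p = 0.0007, as stated. An efficacy of 100% means no cases in the two-dose arm.

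**Chance of an empty arm.** P(0 of 25) = [1 − p₀(1 − VE)]²⁵, where p₀ is the placebo rate and VE the efficacy.

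| Placebo rate | VE 70% | VE 80% | VE 90% | VE 92.1% |
|---|---|---|---|---|
| 20% | 0.213 | 0.360 | 0.603 | 0.672 |
| 30% | 0.095 | 0.213 | 0.467 | 0.549 |
| 40% | 0.041 | 0.124 | 0.360 | 0.448 |
| 50% | 0.017 | 0.072 | 0.277 | 0.365 |
| 60% | 0.007 | 0.041 | 0.213 | 0.297 |

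For example, at 20% and 70% the arm's rate is 0.20 × 0.30 = 0.06, and 0.94²⁵ = 0.213.

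**What the model does with an empty arm.** The empty arm contributes (1 − π)²⁵ to the likelihood. This increases all the way to π = 0, so the log odds ratio has no finite maximum. In a four-group Newton-Raphson fit with 14, 4, 9 and 0 events of 25 (placebo, 15 µg × 2, 30 µg × 1, 30 µg × 2), the coefficient for the empty arm against placebo runs as follows.

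| Iteration | Log OR | SE | Wald p |
|---|---|---|---|
| 8 | −9.44 | 19.9 | 0.64 |
| 15 | −16.44 | 660 | 0.98 |
| 20 | −21.44 | 8,039 | 0.998 |

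The other two contrasts with placebo stay finite and stable, at −1.90 (SE 0.68) and −0.82 (SE 0.58).

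**The same comparison by other tests, 14/25 against 0/25.**
- Fisher, two-sided: 2 × C(25,14)/C(50,14) = 0.0000095.
- Likelihood ratio, two arms: the log-likelihood under a common rate is 14 ln 0.28 + 36 ln 0.72 = −29.65. With separate rates it is 14 ln 0.56 + 11 ln 0.44 = −17.15. Twice the difference is 25.0 on 1 df, p about 6 × 10⁻⁷.

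**Adjusted models with a remedy.** Four arms of 25, with simulated age and gender as covariates; p-values are for 30 µg × 2 against placebo.

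| Events (placebo / 15×2 / 30×1 / 30×2) | Wald, iteration 15 | Ordinary LR | Firth penalised LR | Fisher | Firth OR |
|---|---|---|---|---|---|
| 14/4/9/0 | 0.98 | 9e-7 | 5e-6 | 1e-5 | 0.017 |
| 10/2/5/0 | 0.98 | 4e-5 | 0.0002 | 0.0006 | 0.026 |
| 6/1/3/0 | 0.98 | 0.003 | 0.011 | 0.022 | 0.064 |

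The joint 3-df Wald test of group is weakened too: 0.043, 0.078 and 0.37 in the three rows, against ordinary likelihood-ratio values of 6e-6, 0.0003 and 0.016.

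**The case against.** The strongest reply is that this is detail for an analysis plan. The protocol names a procedure, does not prescribe a Wald test, and does not rule out exact or likelihood-ratio inference within that procedure. It places the model beside chi-square comparisons of the same outcomes, in a phase II trial that it says will not supply definitive evidence. Much of this stands and it limits the weight of the point. What remains is that the protocol chose a method and wrote exactness in for one analysis only, while its own background section reports a result that would defeat the other.

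Four stronger readings are tempting, and the documents do not support them.
- **That the trial would miss a large effect.** It would not. The exact chi-square tests cope with a zero cell, and a likelihood-ratio test from the same model detects the effect.
- **That the only adjusted efficacy analysis would fail.** Section 9.3.8.2 also plans adjusted linear models for tissue counts and viral shedding, and within the logistic model only contrasts with the empty arm diverge.
- **That an empty arm is more likely than not.** A figure of 57% for at least one empty arm follows from active-arm rates of 4.5%, 4.5% and 10%. These are not planning values in the protocol, and the previous one-dose arm had 45.8% any illness. At the protocol's 70% efficacy with a 55% placebo rate, the active rate is 16.5% and P(0 of 25) is 0.835²⁵, about 1% per arm. The 4.5% also came from setting aside physician-observed pharyngitis, which section 9.3.2 counts.
- **That the model is badly overloaded, with eight or more terms.** Titers enter only some models. The base model has about six terms (three for group, one each for age and gender, at least one for race). At 25 × (0.55 + 3 × 0.165) = 26 expected any-illness events, that is about four per term: thin, but a separate and lesser matter.

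The previous zero count is also preliminary, because culture was insensitive. Section 9.3.6 now accepts antigen and molecular detection, which could add cases.

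**Conclusion.** The point holds in a limited form. For illness plus infection, and for rarer illness components, an active arm with no events is foreseeable. For any illness it is much less so, since the previous two-dose arm had about one case in 22. When it happens, the adjusted odds ratio for that arm does not exist, and its Wald interval and p-value carry no information. The unadjusted exact comparisons are untouched.

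The probability cannot be fixed from the protocol. On an assumed placebo rate of 20% to 60% and 25 per arm, it is 21% to 0.7% at 70% efficacy and 67% to 30% at 92.1% efficacy. The exact Wald p depends on where the software stops; the absence of a finite estimate does not. This is a cheap improvement to consider, not a flaw that threatens the trial's conclusions.

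**What to change.** Add to section 9.3.8.2 that the adjusted binary models use Firth penalised-likelihood logistic regression, or exact conditional logistic regression, with profile-likelihood or exact intervals. State that (penalised) likelihood-ratio or exact tests replace Wald tests, at least whenever a group has no events.

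In the same paragraph, keep post-vaccination titers out of the model that estimates the vaccine effect, and use them only in separate correlate-of-protection models. Such a titer is measured after randomisation and lies on the path from vaccine to protection, so adjusting for it can remove part of the effect being estimated. For that reason a pre-challenge antibody term should not be added as a way of simplifying the model. Age, gender and race can stay.

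The cost is a sentence or two, slight shrinkage of the estimates and a little more programming. The change should be made before unblinding, so that the method is not chosen with the results in view.

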### 7.1.10 Challenge Phase Day 0 (39  3 days after First Treatment; Admission to Quarantine):

 All subjects will be admitted to the quarantine unit.

- An interval medical history will be performed to ensure that each subject continues to meet all inclusion and no exclusion criteria (excepting influenza vaccine and serum HAI criteria, which will have become irrelevant due to the immunization component of this protocol).
- Subjects will be queried regarding the occurrence of adverse events and changes in concomitant medications, and the results recorded.
- Subjects will complete an Influenza Symptom Diary Card (see Appendix F), and will be interviewed by a physician re: potential symptoms of influenza or upper respiratory infection.
- A complete physical examination, including vital signs with oral temperature, will be performed and recorded.
- An ECG will be performed.

 A nasal wash specimen for specific antibody assay will be obtained from each subject (see section 7.2).

 Approximately 15 mL of blood will be drawn from each subject for specific HAI serologies (see section 7.2).

7.1.11 Challenge Phase Day 1:

 Subjects will have oral temperature measured and recorded four times a day.

- Subjects will complete an Influenza Symptom Diary Card (see Appendix F), and will be interviewed by a physician, approximately every 12 hours.
- Subjects will be queried regarding occurrence of AEs not specified in the Influenza Symptom Diary Card, and these will be recorded.
- A directed physical examination using the Challenge Physical Examination Worksheet (see Appendix G) will be performed and recorded in the evening.
- Subjects will be instructed in, and begin, collection of used tissues for 24 hour-counts and weights.
- Any subject with grade 2 findings or complaints and/or an oral temperature ≥ 37.9 º C (confirmed by repetition at an interval of not less than 20 minutes) will be immediately segregated from the remaining subjects and discharged if any suspicion of an **intercurrent** respiratory infection exists. The examining physician will provide medical referral for outpatient care if deemed necessary. The cause of such discharge will be recorded as an adverse event. The subject will be instructed to return for the day 60 outpatient visit.

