### 7.3.3 Temperature Measurements During the Challenge Phase:

From Challenge Phase Day 1 to Day 9, oral temperature will be recorded at least four (4) times daily. Because these readings are critical to definitions of illness and to symptomatic and specific therapy criteria, temperatures of ≥ 37.6ºC must be confirmed by a repeat measurement not less than 20 minutes and not more than 60 minutes after the first reading. Subjects will be instructed not to eat or drink during the interval between the two measurements.

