## 9.3 Illness Definitions and Analysis for Challenge Component:

9.3.1 Fever:

Fever will be defined as any oral temperature 37.9C which is confirmed by a repeat observation at an interval of not less than 20 minutes and not more than 60 minutes. Prior experience has shown that electronic digital thermometers used in climate-controlled environments may not precisely reflect the normal oral temperature range established in the era of mercury bulb instruments used in ambient conditions. Accordingly, an alternative definition of fever, i.e., ≥ 3 standard deviations above the mean of the third temperature observation on **Challenge** Phase Day 1, will be utilized if significantly lower than 37.9º C.

9.3.2 Upper Respiratory Illness:

A subject will be considered to have upper respiratory illness if he or she has any one of the following on two (2) consecutive days, at least one (1) day of which must feature grade 2 severity, or if any of the following attain grade 3 severity once:

- Self-reported symptoms:
  - Rhinorrhea (runny nose), or
  - Nasal congestion (stuffy nose), or
  - Sore throat.
- Physician findings:
  - Nasal discharge
  - Otitis
  - Sinus tenderness
  - Pharyngitis

9.3.3 Lower Respiratory Illness:

A subject will be considered to have upper respiratory illness if he or she has any one of the following on two (2) consecutive days, at least one (1) day of which must attain grade 2 severity, or if any of the following attain grade 3 severity once:

- Self-reported symptoms:
  - Cough, or
- Physician findings:
  - New wheezing, rhonchi, râles, or signs of consolidation

9.3.4 Systemic Illness:

A subject will be considered to have upper respiratory illness if he or she has any one of the following on two (2) consecutive days, at least one (1) day of which must attain grade 2 severity, or if any of the following attain grade 3 severity once:

- Headache
- Myalgia and/or athralgia

9.3.5 Illness (Any):

A subject will be considered to have illness if he/she fulfills the criteria for fever, or upper respiratory illness, or lower respiratory illness, or systemic illness or any combination thereof.

9.3.6 Infection:

A subject will be deemed to be infected if he/she has any one of:

- Influenza virus shedding in nasal wash at any level, or
- Detection of influenza virus in the throat swab by using **culture, antigen detection or** molecular biology techniques, or

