Additional secondary analyses will be based on tissue counts (and weights, if feasible) as a marker of illness severity, and on virus shedding assessed by two methods: peak and a time-weighted average calculated as a trapezoidal-rule AUC. For both peak and AUC, viral shedding is in units of log10 (titer). These continuous data will be compared between cross-over groups by Student’s t-tests and Wilcoxon tests and, in a more flexible analysis, by linear model adjusted for the demographic and clinical covariates cited above.

Finally, the three binary measures of influenza and the two viral load estimates (peak titer and AUC) will be assessed relative to the two immunologic measures, HAI reciprocal titer and nasal secretory IgA. For the binary measures, mean viral load (for each measure) is compared by t-tests between those with and without influenza (for each definition). For the two immunologic measures, the test of association with viral load will be based on Pearson correlations of log-titers.

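### The tissue-count comparison in Section 9.3.8.2 omits the subject's own pre-inoculation tissue value, which is already collected and could add precision

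*Protocol*

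**What the plan says.** Protocol Section 9.3.8.2 introduces the outcome: "Additional secondary analyses will be based on tissue counts (and weights, if feasible) as a marker of illness severity". Virus shedding, as peak and AUC, is named in the same sentence. The methods follow: "These continuous data will be compared between cross-over groups by Student’s t-tests and Wilcoxon tests", and, as a more flexible analysis, a comparison "by linear model adjusted for the demographic and clinical covariates cited above". The covariates referred to are listed earlier in the same section: "Covariates are cross-over study group, age, gender, race, and, for some models, titers after vaccinations 1 and 2".

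The pre-inoculation data come from Section 7.1.11 (Challenge Phase Day 1): "Subjects will be instructed in, and begin, collection of used tissues for 24 hour-counts and weights". Appendix B, Table B.2 schedules 24-hour tissue counts on Challenge Phase Days 1 to 9. Section 7.1.12 places inoculation on the morning of Day 2.

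Elsewhere the protocol does adjust for earlier values of the same measure. Section 9.1 provides for baseline titer as a covariate for antibody fold-rise, and Section 9.2.2 for dose 1 outcomes when dose 2 reactogenicity is compared.

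**The concern.** The covariate list is stated rather than left open, and it omits the one measurement of the outcome itself taken before challenge. Subjects may differ in how many tissues they use when well. If that difference persists after inoculation, it adds to the within-group variance of the severity marker, and a pre-inoculation covariate would remove part of it. Section 9.3.8.1 says the variability of the continuous outcomes is not known in advance, and groups of about 25 are small. What is at stake is precision in a secondary analysis.

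A related gap is that neither Section 5.2 nor Section 9.3.8.2 says which collection days form the tissue outcome. Day 1 collections, which cannot reflect the challenge, are not expressly excluded.

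**Working it through.** **The plan's own figure.** The protocol states no power for any continuous outcome. Its only challenge-phase figure (Section 9.3.8.1) is at least 0.80 power for a 70% reduction in any illness with 28 per group. A pooled z calculation gives 0.816, 0.873 and 0.919 at control rates of 50%, 55% and 60%, so that figure reproduces. It does not bear on tissue counts.

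**Inputs.**
- n = 25 challenged per group (Section 4.1, approximate).
- Two-sided alpha 0.05 (Section 9.0).
- r, the correlation between the Day 1 and post-challenge tissue values within group: not in the documents. Assumed range 0 to 0.8.
- Difference d in units of the within-group SD. The documents give no SD, so d is set to the value with 80% unadjusted power.

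**Unadjusted t-test.** Noncentrality = d / √(2/n), with 2n − 2 = 48 degrees of freedom. Power of 0.80 needs d = 0.809: 0.809 / √(2/25) = 0.809 / 0.283 = 2.86.

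**Linear model with the Day 1 value.** The residual variance is multiplied by (1 − r²) and one degree of freedom is lost (47). Noncentrality = 2.86 / √(1 − r²). At r = 0.5, for example, 2.86 / √0.75 = 3.30. Equivalent unadjusted n = 25 / (1 − r²).

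| Assumed r | Variance factor 1 − r² | Power at d = 0.809 | d with 80% power | Equivalent n per group |
|---|---|---|---|---|
| 0 | 1.00 | 0.80 | 0.81 | 25.0 |
| 0.3 | 0.91 | 0.835 | 0.77 | 27.5 |
| 0.5 | 0.75 | 0.899 | 0.70 | 33.3 |
| 0.7 | 0.51 | 0.975 | 0.58 | 49.0 |
| 0.8 | 0.36 | 0.997 | 0.49 | 69.4 |

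**Covariate rather than change score.** Analysing change from Day 1 multiplies the variance by 2(1 − r). That factor is 1.4 at r = 0.3 and 1.0 at r = 0.5, so a change score loses precision whenever r is below 0.5. The covariate loses only the one degree of freedom, even at r = 0.

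**Day 1 as a baseline.** Day 1 falls after randomisation, so adjustment assumes that vaccination no longer affects tissue use by then. Admission is on day 39 ± 3, so Day 1 is day 37 at the earliest. The second dose is given by day 21 at the latest (Section 7.1.6), and 37 − 21 = 16 days. Section 1.0 reports that vaccine nasal symptoms typically last one to three days. The assumption is therefore reasonable.

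**The case against.** The t and Wilcoxon tests are valid as they stand. The outcome is secondary, and Section 9.0 says the trial is not meant to give definitive evidence. The benefit rests wholly on an unstated correlation, which the design may keep low. Section 4.3 excludes chronic and recent users of rhinitis or congestion products. Sections 5.2, 7.1.11 and 7.1.12 provide, in differing terms, for discharging subjects who become symptomatic before inoculation. Day 1 tissue use may therefore sit near zero and predict challenge-induced rhinorrhea poorly. The Day 1 value may also be imperfect. Subjects are instructed and start collecting during that day, with no stated hour, so it could cover a partial day or a 24-hour window that runs past inoculation. A plain log transform would fail on zero counts. All of this stands. It limits the likely gain and shapes the fix, but it does not remove the case for a covariate that costs one degree of freedom.

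Three stronger readings are tempting and are not supported:

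- **Mean temperature is fixed as an unadjusted comparison.** Section 9.3.8.1 mentions "continuous outcomes (e.g., treatment group mean temperatures, tissue counts, peak viral shedding and shedding AUC, etc" only as examples. The Section 9.3.8.2 methods quoted above refer to tissue measures and shedding, and no temperature comparison is specified there.
- **Thermometer differences obscure the contrast.** Sections 1.0 and 9.3.1 describe a shift in the temperature scale. A shift common to all groups cancels between them, and no between-device or between-subject spread is given. Section 9.3.1 already uses Day 1 readings for the alternative fever threshold, "≥ 3 standard deviations above the mean of the third temperature observation on" Challenge Phase Day 1.
- **Differences between subjects overwhelm the severity contrast, or Day 1 tissues are counted in it.** No SD, effect size or correlation is given to support the first. For the second, the text does not rule it out, but nothing says it will be done.

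**Conclusion.** The point holds for tissue counts and weights. The stated covariate list leaves out a pre-inoculation value that the schedule already provides. Because groups are randomised, the omission does not bias the comparison; it may lose precision. At 25 per group, power for a difference with 80% unadjusted power would be about 84%, 90% or 98% at an assumed correlation of 0.3, 0.5 or 0.7, with no gain at 0. These figures assume an approximately linear relation, a common within-group variance and a Day 1 value unaffected by vaccination. The documents do not show where in this range the correlation lies, and a low value is plausible. This is a free improvement to a secondary outcome, not an error that threatens the trial's conclusions.

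**What to change.** In Section 9.3.8.2:

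1. Define the tissue outcome on post-inoculation collections only.
2. Define the Day 1 collection window so that it ends before inoculation and is the same for all subjects.
3. Add the subject's own Day 1 tissue count (or weight, when weight is the outcome) as a covariate in the linear model. If the data are skewed, use a transformation that allows zeros, such as log(count + 1).
4. Keep the t and Wilcoxon tests.
5. If mean temperature is analysed, state its summary and adjust for the subject's own Day 1 mean. The readings exist under Section 7.3.3: "From Challenge Phase Day 1 to Day 9, oral temperature will be recorded at least four (4) times daily".

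The cost is analysis wording, a stated collection window and one degree of freedom. No new measurement or visit is needed.
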